
### Randomization

Random sequence generation (computer generated, using block randomisation) will be performed and allocation will be concealed. An allocation ratio of 1:1.15 will be applied (130 patients allocated to immediate ACL reconstruction and 150 patients allocated to conservative treatment). With this we comply with the sample size calculation. We will have (1) minimum 130 patients per arm for the primary analysis and (2) 150 patients in the conservative arm for the secondary analysis. At each participating site, the responsible study nurse/principal investigator will have access to the randomisation tool in REDCap.

To ensure the integrity of the Trial: the randomization list will be prepared by a statistician not involved in the trial. The randomization list will be incorporated in the data management tool ‘REDCap’. After all patients have finished the Trial and the database is locked, the randomization code will be broken for analysis of response data.

### Blinding

Given the nature of the trial, blinding of participants and care providers is not feasible.

Data collectors and data analysts will be blinded to the extent possible. Outcomes will be collected in the same way in both groups, e.g. by electronical questionnaires for which assessors and collectors can be blinded. However, because of the subjective and self-reported nature of the outcomes being assessed, detection bias may be a potential risk of bias. After all participants have completed the Trial, the database will be locked and the collected Trial data will be unblinded to allow analysis of the Trial data.

### Statistical analyses

The primary analyses will be performed on the intention-to-treat (ITT) population (subjects are included in the groups to which they were randomly assigned, even if they did not complete their treatment). For example, subjects in the conservative group that underwent ACL reconstruction or subjects in the early reconstruction group that did not undergo reconstruction. This choice was based on the main aim of this trial: informing medical doctors which strategy (immediate ACL reconstruction or conservative with optional delayed surgery) is most appropriate after acute ACL injury and therefore help them in decision-making to undergo immediate ACL reconstruction or not. This ITT analysis will closely reflect everyday practice as in real life; patients will not always adhere to either therapy’s advice.

The as-treated population includes subjects in groups as to how they were treated. This post- hoc as-treated analysis will result in 3 groups: rehabilitation alone, rehabilitation plus early ACL reconstruction, and rehabilitation plus delayed ACL reconstruction. However, this analysis will only be explorative as this will be a non-randomized comparison that will probably be biased.

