
Based on the results of the KANON trial [1] and the COMPARE trial [2] one can conclude that conservative management with optional delayed surgery does not result in inferior clinical outcomes compared to immediate ACL reconstruction on a population level [14].

Though, on the level of the individual patient, large between-subject differences were found. In the KANON trial, 39% of the ACL patients in the conservative treatment group showed persistent knee instability requiring delayed surgery during the two years follow up, this percentage has grown to 51% at the five years follow up [1, 13]. The compare trial reported that 50% of the ACL patients in the conservative group required delayed surgery in the two years follow up [2]. In this group of patients, time to return-to-sport is extended, and longer sick leave times are observed because surgery is delayed compared to patients undergoing immediate ACL reconstruction [15]. Hence, early identification of patients who would benefit from early ACL reconstruction, or on the contrary, from rehabilitation alone, is crucial to reduce resource consumption and decrease irrelevant overtreatment. It is hypothesized that treatment success relies on clinical factors (such as knee function and MRI features [16] ) as well as the quality of rehabilitation [17], and psychological factors such as expectations [18], fear of re-injury [19, 20] and locus of control [21].

This large RCT has 2 aims: (1) to compare the clinical effectiveness of both treatment options and as such verify the existing literature, and (2) to assesses which patient-specific factors predict successful outcomes after conservative treatment of ACL injuries.

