#### Indications for delayed surgery

If a patient of the conservative treatment group complains about consistent symptomatic instability of the knee that prevents rehabilitation progression, a delayed surgery can be considered. A positive pivot shift in combination with ACL insufficiency-induced instability and an additional MRI are needed to confirm the cause of instability (Criteria based on the KANON trial [1]). According to current practice, delayed surgery will not be performed within the first 12 weeks post-injury.

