#### Primary outcome analysis

The primary analysis will compare the intervention group with the control group on their mean change in KOOS QOL at 2 primary endpoints:

Non-inferiority testing at 1 year post-injury.Superiority testing at 7 months post-injury.

A one-sided 95% confidence interval for the mean difference between groups excluding 7 units in the disadvantage of the conservative treatment will be considered as a demonstration of non-inferiority at 1 year. A two-sided 95% confidence interval for the mean difference between groups excluding 13.5 units in the advantage of the conservative treatment will be considered as a demonstration of superiority at 7 months.

Estimation and testing of these mean differences will be based on a single analysis model. A linear model for repeated measurements will be used, applied to outcome measures at all time points, modelling an unstructured residual variance-covariance matrix to deal with correlations due to the longitudinal data structure. Compared to separate cross-sectional analyses, this approach improves the power and minimizes the effects of possible bias due to drop-out. All patients with at least one outcome measurement are included in the analysis, even if they had no outcome measured at 7 or 12 months. The model includes group, time-point and group by time-point interaction as effects. The mean differences between the groups at 7 and 12 months and their confidence intervals will be estimated as post-hoc tests based on this model. Given the hierarchical approach of statistical testing (superiority testing only if non-inferiority is demonstrated), no correction for multiple testing will be performed.

The primary analysis will be applied to the ITT population. Patients without outcome measures apart from baseline will be excluded.

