#### Explorative analysis

A similar method of analysis as described for the primary analysis (intention-to-treat) will be applied to the as-treated analyses.

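### The as-treated analysis does not say when treatment status is fixed; read naturally, it labels 7- and 12-month KOOS scores by later surgery, a minor but avoidable bias

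*Protocol article*

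**What the plan says.** All references are to the protocol article.

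- **Statistical analyses** defines the groups: "The as-treated population includes subjects in groups as to how they were treated". It continues: "This post- hoc as-treated analysis will result in 3 groups: rehabilitation alone, rehabilitation plus early ACL reconstruction, and rehabilitation plus delayed ACL reconstruction". It adds that "this analysis will only be explorative as this will be a non-randomized comparison that will probably be biased".
- **Explorative analysis** gives the method: "A similar method of analysis as described for the primary analysis (intention-to-treat) will be applied to the as-treated analyses".
- **Primary outcome analysis** describes that method, a repeated-measures model over all time points: "The model includes group, time-point and group by time-point interaction as effects". From it, "The mean differences between the groups at 7 and 12 months and their confidence intervals will be estimated".
- **Indications for delayed surgery** sets the earliest time ("delayed surgery will not be performed within the first 12 weeks post-injury") and makes persistent symptomatic instability that blocks rehabilitation progress the reason for considering surgery. Table 2 marks optional delayed surgery as possible at every follow-up visit from 4 to 36 months.
- **Randomization** and **Blinding** place the analysis after all participants have completed the trial.

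None of these sections gives a date or visit at which as-treated status is determined.

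**The concern.** The primary model has one group factor. If the three treatment-received groups simply replace the randomized arms in it, each patient carries one label through all visits. With analysis after 36 months, that label reflects everything that happened by then. The 7- and 12-month contrasts would then sort patients by an event that may lie after the score being compared.

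The direction of the resulting bias can be predicted. Instability is the indication for delayed surgery, and the Secondary objective section itself expects patients with high KOOS QOL to need it less often. Taking future surgical patients out of the rehabilitation-alone group at month 7 or 12 therefore removes patients who tend to be doing worse. At that moment they have received the same treatment as those who stay in the group.

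The protocol's caveat attributes the expected bias to the lack of randomization. Sorting on future surgery is a separate source, and a grouping rule can remove it. At stake is the reading of an exploratory result that clinicians may consult when judging how patients fare without surgery.

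**Working it through.** **Plan's own figure.** The Sample size section expects one third of the conservative arm to need delayed surgery and wants 50 events: 50 / (1/3) = 150. This reproduces exactly. The check uses M = 50 delayed surgeries among N = 150 conservative patients. Immediate-arm patients who are never operated on are left out.

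**Timing (assumed).** The documents give no surgery rates at 7 or 12 months. Take surgeries between week 12 (2.76 months) and month 36.
- Even spread: (12 − 2.76)/33.24 = 27.8%, so 14 of 50 by month 12; (7 − 2.76)/33.24 = 12.8%, so 6 of 50 by month 7.
- Front-loaded: an exponential with median 6 to 12 months after week 12, truncated at month 36, gives 67% to 48% by month 12 (34 to 24 of 50) and 40% to 25% by month 7 (20 to 13 of 50).

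The even spread fits the cited evidence poorly. Background reports 39% operated on by two years in an earlier trial, and "this percentage has grown to 51% at the five years follow up". That is 39/2 = 19.5 percentage points a year, then (51 − 39)/3 = 4 a year. The even spread is kept only as the upper end.

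**Selection model (assumed).** KOOS QOL change has correlation r = 0.3 to 0.7 with a standard normal liability to surgery. The worst third is eventually operated on, and surgery has no effect. The mean liability is +0.545 in the upper two thirds and −1.091 in the lower third, a gap of 1.636. SDs are the plan's: 19 at 12 months and 18 at 7 months.

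**Total selection under a fixed label.** The rehabilitation-alone group is lifted, relative to the whole arm, by 0.545 × 19 × r = 3.1 to 7.3 points at 12 months.

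**Part due to the label alone.** Let k patients have been operated on before the visit, taken as a random subset of the M. Visit-specific grouping puts the other M − k back into the rehabilitation-alone group, which then has N − k members. The avoidable lift is

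lift = [(M − k) / (N − k)] × 1.636 × SD × r

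| Visit | k | (M − k)/(N − k) | Lift, r = 0.3 | Lift, r = 0.7 |
|---|---|---|---|---|
| 12 months | 34 | 16/116 | 1.3 | 3.0 |
| 12 months | 24 | 26/126 | 1.9 | 4.5 |
| 12 months | 14 | 36/136 | 2.5 | 5.8 |
| 7 months | 20 | 30/130 | 2.0 | 4.8 |
| 7 months | 6 | 44/144 | 2.7 | 6.3 |

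In this model the operated group has the same mean under either rule, so the lift is also the change in the contrast between rehabilitation alone and delayed reconstruction.

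**Sensitivity to the surgery rate.** Interpolating the earlier trial's 39% and 51% gives about 65 of 150 by month 36, with 23 to 36 of them after month 12. The liability gap becomes 0.694 + 0.908 = 1.602. The lift runs from 23/108 × 1.602 × 19 × 0.3 = 1.9 to 36/121 × 1.602 × 19 × 0.7 = 6.3 points, the same order of size.

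**The case against.** The strongest reply is that no sentence fixes one label per patient. Calling the method similar leaves room for a landmark or visit-specific rule in an analysis plan that is not shown, and the article condenses a longer protocol. This stands as a limit: the fixed label is an inference. It is nevertheless the reading to which the three sections lead, because the model they point to has a single group factor and nothing time-varying.

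Second, the analysis is declared exploratory and probably biased, and no hypothesis, decision rule or sample size depends on it. This also stands, and it keeps the point minor. It does not make an avoidable bias harmless.

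Third, a reader might attribute the full 3.1 to 7.3 points to the label, or set them against the 7-point non-inferiority margin. The documents support neither. Much of that lift comes from patients operated on before the visit, whom any as-treated grouping removes. The margin belongs to the intention-to-treat test at 1 year, and nothing applies it to the three as-treated groups.

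Fourth, describing trajectories by eventual treatment is a legitimate question, close to the secondary aim of learning who comes to need surgery. That is right, provided it is presented as description and not as a comparison of treatments at 7 or 12 months.

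**Conclusion.** The point holds as a minor one. The natural reading of the as-treated plan conditions the 7- and 12-month contrasts on later surgery and flatters rehabilitation alone.

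With one third eventually operated on, 14 to 34 of 50 surgeries by month 12 and r of 0.3 to 0.7, the avoidable lift at 12 months is about 1.3 to 5.8 points. It is 1.3 to 4.5 under the front-loaded timing that the cited rates favour. The direction rests on the protocol's own indication for surgery. The size rests on assumed timing, an assumed correlation, no surgical effect, and early surgeries being a random subset of all delayed ones. Confounding by past symptoms comes on top and remains under any labelling rule.

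A reader might infer that the trial's main conclusion is at risk. It is not: the primary analysis follows randomized groups and does not use this label.

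**What to change.** In Statistical analyses and Explorative analysis, state that as-treated status for each visit's contrast is determined by surgery performed before that KOOS date, through visit-specific or landmark grouping. Conservative patients not yet operated on at a visit then count as rehabilitation alone at that visit. Report the time from surgery to KOOS for the operated groups. If results by eventual treatment are also shown, label them descriptive only.

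No new data should be needed, since surgery details are already recorded in the patient register. The cost is somewhat more than wording. Group sizes will differ by visit, and the model needs a visit-specific group term or separate landmark analyses. The existing caveat must stay, because selection on earlier symptoms remains.

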#### Primary outcome analysis

The primary analysis will compare the intervention group with the control group on their mean change in KOOS QOL at 2 primary endpoints:

Non-inferiority testing at 1 year post-injury.Superiority testing at 7 months post-injury.

A one-sided 95% confidence interval for the mean difference between groups excluding 7 units in the disadvantage of the conservative treatment will be considered as a demonstration of non-inferiority at 1 year. A two-sided 95% confidence interval for the mean difference between groups excluding 13.5 units in the advantage of the conservative treatment will be considered as a demonstration of superiority at 7 months.

Estimation and testing of these mean differences will be based on a single analysis model. A linear model for repeated measurements will be used, applied to outcome measures at all time points, modelling an unstructured residual variance-covariance matrix to deal with correlations due to the longitudinal data structure. Compared to separate cross-sectional analyses, this approach improves the power and minimizes the effects of possible bias due to drop-out. All patients with at least one outcome measurement are included in the analysis, even if they had no outcome measured at 7 or 12 months. The model includes group, time-point and group by time-point interaction as effects. The mean differences between the groups at 7 and 12 months and their confidence intervals will be estimated as post-hoc tests based on this model. Given the hierarchical approach of statistical testing (superiority testing only if non-inferiority is demonstrated), no correction for multiple testing will be performed.

The primary analysis will be applied to the ITT population. Patients without outcome measures apart from baseline will be excluded.

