### Sample size

The outcome(s) on which the sample size calculation is based upon is the KOOS QOL, a self-administered questionnaire. The outcome for the **non-inferiority analysis** is the change on the KOOS QOL between the baseline measurement and 1 year after randomization. The sample size was calculated using the power procedure in SAS 9.4 to show with 80% of power that conservative treatment is not inferior to standard treatment, where a non-inferiority margin of 7 (change-points) was adopted based on the study of Collins et al. who report a minimal detectable change in KOOS QOL of 7 points [33]. The analysis consists in estimating the difference in mean change-scores between both treatment arms with a one-sided 95% confidence interval (Corresponding to a 5% significance level). Non-inferiority will be concluded when the lower limit of the confidence interval will be above the non-inferiority margin of -7. An equal treatment effect in both arms and a standard deviation for the change-score of 19 were assumed for the sample size calculation [1]. Assuming a drop-out of 10%, a total number of 260 patients is required for randomization. For the **superiority analysis** the sample size was calculated to demonstrate with a two-sample t-test a difference between the two treatment groups with respect to the change in KOOS QOL score at 7 months follow-up compared to post-injury. Considering equal group sizes, a two-sided 5% significance level, 90% power, the smallest important difference as 13.5 change-points [31] a standard deviation of 18 for the change in KOOS QOL versus baseline [31], and a 10% drop-out rate, the calculation indicates a total sample size of 88 patients. Furthermore, the 5% significance level was adopted since a hierarchy of statistical testing will be used. Only if the non-inferiority test is significant at 12 months, the test of superiority at 7 months will be performed since superiority is judged necessary to change practice. Furthermore, a prediction model will be built in the intervention group (rehabilitation and optional delayed ACL reconstruction) with the event of delayed surgery as binary outcome and where an initial set of the five predictor variables described above will be considered. Following the rule of thumb of including at least 10 events per parameter in the model, this analysis requires at least 50 events (i.e. delayed surgeries in the experimental group). Assuming that 1/3 of patients in the experimental group will need delayed surgery (KANON Trial), a minimum of 150 patients will be needed in the intervention group in order to develop such a prediction model.

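### The 7-month superiority rule uses 13.5 points as the boundary the confidence interval must clear, but the sample size uses 13.5 as the assumed true difference in a test against zero

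*Protocol article*

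**What the plan says.** Three sections of the protocol article bear on the 7-month comparison.

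- **Objectives, Primary objective.** The hypothesis is that the optional delayed surgery approach gives better patient-reported outcomes than immediate reconstruction at 7 months. No minimum margin is attached.
- **Sample size.** The superiority calculation was done "to demonstrate with a two-sample t-test a difference between the two treatment groups" in change in KOOS QOL. Its inputs are "Considering equal group sizes, a two-sided 5% significance level, 90% power", "the smallest important difference as 13.5 change-points" and "a standard deviation of 18 for the change in KOOS QOL versus baseline". It ends "and a 10% drop-out rate, the calculation indicates a total sample size of 88 patients". The test is performed only if 12-month non-inferiority has been shown, and the section treats superiority as needed to change practice.
- **Statistical analyses, Primary outcome analysis.** Superiority at 7 months is demonstrated by "A two-sided 95% confidence interval for the mean difference between groups excluding 13.5 units in the advantage of the conservative treatment". The sentence before it gives the 12-month rule in the same form, with 7 units against conservative treatment. The Sample size section spells out that rule as a lower confidence limit above -7.

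**The concern.** The same 13.5 points has two incompatible roles. In the sample size it is the effect assumed to be true, tested against a null of zero. In the analysis rule it is the null boundary itself. If the boundary equals the planned effect, the trial can hardly ever succeed when its planning assumption is exactly right.

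This is one of two primary tests, and the one the protocol ties to a change of practice. A plausible result shows what is at stake. An observed advantage of 10 points, with an interval of about 5.5 to 14.5 (half-width 4.48, derived in the working), is superior under the hypothesis and the sample size section but not under the analysis rule. Left alone, the verdict would depend on which section is followed once the results are known.

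**Working it through.** **Inputs.** True difference 13.5, SD 18, two-sided 5%, 90% power and 10% drop-out come from Sample size. The allocation of 130 to immediate reconstruction and 150 to conservative treatment comes from Randomization. Applying the 10% drop-out to each arm is an assumption: 130 × 0.9 = 117 and 150 × 0.9 = 135.

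**Step 1: reproduce the 88.** A two-sample t-test against zero (noncentral t) has power 89.7% with 38 per arm and 90.5% with 39 per arm. So 39 per arm are needed; 39 / 0.9 = 43.3, rounded up to 44 per arm, or 88 in total. The stated figure is reproduced with a null of zero.

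**Step 2: power under the analysis rule at the planning assumption.** Writing D for the true difference,

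P(lower limit > 13.5) = 1 − Φ(1.96 − (D − 13.5)/SE).

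At D = 13.5 the SE drops out: 1 − Φ(1.96) = 2.5%. This holds for any sample size and any SE. Because 12-month non-inferiority must be shown first, 2.5% is an upper bound.

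**Step 3: size at the planned sample.**

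- SE = 18 × √(1/117 + 1/135) = 2.27.
- With 250 degrees of freedom the half-width of the interval is 4.48.
- Observed difference needed to clear 13.5: 13.5 + 4.48 = 17.98, about 18.0.
- Observed difference needed to clear 0: about 4.5.
- True difference for 90% power under the 13.5 rule: 13.5 + (1.96 + 1.2816) × 2.2736 = 20.87, about 20.9.

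| True difference | Power, lower limit > 13.5 | Power, lower limit > 0 |
|---|---|---|
| 13.5 | 2.5% | >99.9% |
| 15 | 9.7% | >99.9% |
| 18 | 51% | >99.9% |
| 20 | 82% | >99.9% |

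The table ignores the preceding 12-month gate, which can only lower these figures.

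**Step 4: sensitivity to the evaluable number (SD 18).**

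| Evaluable | SE | Observed difference needed to clear 13.5 | True difference for 90% power |
|---|---|---|---|
| 39 + 39 | 4.08 | 21.6 | 26.7 |
| 117 + 117 | 2.35 | 18.1 | 21.1 |
| 117 + 135 | 2.27 | 18.0 | 20.9 |
| 130 + 150 (no drop-out) | 2.16 | 17.7 | 20.5 |

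The planned analysis is a repeated-measures model, which may have a smaller SE than this cross-sectional one. That would lower the last two columns somewhat but would leave the 2.5% in Step 2 unchanged.

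**The case against.** **A clinically important margin may be intended.** The Sample size section calls 13.5 the smallest important difference and links superiority to changing practice. Requiring the interval to lie beyond that value is a legitimate criterion. A rule based on zero could declare superiority at an observed 4.5 points, below the minimal detectable change of 7 to 7.2 given under Primary outcomes. This stands as a reason not to assume which rule was meant. It does not remove the conflict: if the margin is intended, the hypothesis omits it and the power statement does not describe the test.

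**The 90% is not the power of the planned trial.** A reader might infer that power falls from 90% to 2.5%. The documents do not support that comparison. The 90% belongs to the calculation giving 88 patients. The planned 280 follows from the non-inferiority requirement (260) and the prediction model (150 in the conservative arm), and at that size power against zero exceeds 99.9%. The 2.5% is simply the tail probability whenever the true effect equals the margin.

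**The rule read literally.** A reader might also infer that an interval lying wholly below 13.5, even one around zero, would satisfy the rule. The wording requires an advantage for conservative treatment and speaks of demonstrating superiority. The parallel 12-month rule is defined elsewhere as a lower limit above its margin. The sensible reading is therefore a lower limit above 13.5.

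**Limited reach.** The 12-month non-inferiority test, the model, the estimate and its interval are unaffected. Only the verdict on the gated 7-month test changes. That is correct, but that verdict is one of the trial's two primary conclusions.

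**Conclusion.** The contradiction stands: either the decision rule or the power statement for the 7-month test is wrong as written. The finding that success has a probability of at most 2.5% at a true 13.5 rests only on reading the rule as a lower limit above 13.5, and holds at any sample size. The figures of about 18.0 observed points and a true difference of about 20.9 for 90% power also assume SD 18, 10% drop-out in each arm and a simple two-group SE; they are illustrative. The documents do not settle which criterion was intended, although the hypothesis and the sample size section both point to a test against zero.

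**What to change.** Make the Primary objective, Sample size and Primary outcome analysis sections agree before the data are unblinded.

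- **Preferred, because it matches the hypothesis and the sample size calculation:** conclude superiority at 7 months if the lower limit of the two-sided 95% confidence interval for the difference in mean change (conservative minus immediate) is above 0. Then interpret the estimate and interval against the 13.5-point smallest important difference. That second step guards against over-reading a small but significant difference.
- **If superiority by a 13.5-point margin is intended:** state the margin in the hypothesis. Replace the 90% power and 88-patient statement with the power at the planned sample size for a stated true difference above 13.5. Quoting the 2.5% at a true 13.5 would not be a usable design statement.

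Cost: recruitment has been running since March 2023, so changing a primary success criterion calls for a formal amendment under Protocol amendments, with steering committee agreement, a registry update and ethics approval. No additional patients or data are needed.
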